## Appendix M: WHO Quality of Life Instrument

**AYUSH COVID-19 PATIENT PROTOCOL 2020**

**WHO- Quality of Life Instrument**

**WHOQOL-BREF**

PATIENT NO: ________________PATIENT INITIALS :_____________DATE:__________

Before you begin we would like to ask you a few general questions about yourself: By circling the correct answer or by filling in the space provided.

What is your **gender** ? Male Female

What is you date of **birth**? _______/_______/_______

Day / Month / Year

What is the highest **education** you received ? None at all

Primary school

Secondary school

Tertiary

What is your marital status ? Single Separated

Married Divorced

Living as married Widowed

Are you currently ill ? Yes No

If something is wrong with your health what do you think it is? ________________ illness. Problem

**Instructions**

This assessment asks how you feel about your quality of life. Health, or other areas of your life. **Please answer all the questions.** If you are unsure about which response to give, **please choose the one** that appears most appropriate. This can often be your first response.

Please keep in mind your standard, hopes, pleasures and concerns. We ask what you think about life in **the last two weeks.** Please read each question, asses your feeling, and circle the number on the scale for each question that gives the best answer for you.

|  | |  | **Very poor** | **Poor** | **Neither poor or good** | **Good** | **Very good** |
| --- | --- | --- | --- | --- | --- | --- | --- |
| 1(G1) | | How would you rate your quality of life? |  |  |  |  |  |
|  | |  |  |  |  |  |  |
|  | |  | **Very dissatisfied** | **dissatisfied** | **Neither satisfied nor dissatisfied** | **Satisfied** | **Very satisfied** |
| 2(G4) | | How satisfied are you with your health ? |  |  |  |  |  |
|  | | | | | | | |
| The following questions ask about how much you have experienced certain things in the last two weeks. | | | | | | | |
|  | |  | **Not at all** | **A little** | **A moderate amount** | **Very much** | **As extreme amount** |
| 3(F1.4) | | To what extent do you feel the physical pain prevents you from doing what you need to do ? |  |  |  |  |  |
| 4( F11.3) | | How much do you need any medical treatment to function in your daily life ? |  |  |  |  |  |
| 5(F4.1) | | How much do you enjoy life ? |  |  |  |  |  |
| 6(F24.2) | | To what extent do you feel your life to be meaningful? |  |  |  |  |  |
|  | |  |  |  |  |  |  |
|  | |  | **Not at all** | **A little** | **A moderate amount** | **Very much** | **Extremely** |
| 7(F5.3) | | How well are you able to concentrate ? |  |  |  |  |  |
| 8(F16.1) | | How safe do you feel in your daily life? |  |  |  |  |  |
| 9(F22.1) | | How healthy is your physical environment ? |  |  |  |  |  |
| The following question ask about how completely you experience or were able to do certain things in the last two weeks. | | | | | | | |
|  |  | | **Not at all** | **A little** | **Moderately** | **Mostly** | **Completely** |
| 10(F2.1) | Do you have enough energy for everyday life ? | |  |  |  |  |  |
| 11(F7.1) | Are you able to accept your bodily appearance ? | |  |  |  |  |  |
| 12(F18.1) | Have you enough money to meet your needs? | |  |  |  |  |  |
| 13(F20.1) | How available to you is the information that you need in your day-to-day life | |  |  |  |  |  |
| 14(F21.1) | To what extent do you have the opportunity for leisure activities ? | |  |  |  |  |  |
|  |  | |  |  |  |  |  |
|  | | | | | | | |
|  |  | | **Very poor** | **Poor** | **Neither poor nor good** | **Good** | **Very good** |
| 15(F9.1) | How well are you able to get around ? | |  |  |  |  |  |
| The following question ask to you say how good or satisfied you have felt about various aspects of your life over the last two weeks | | | | | | | |
|  | |  | **Very dissatisfied** | **Dissatisfied** | **Neither satisfied nor dissatisfied** | **Satisfied** | **Very satisfied** |
| 16(F3.3) | | How satisfied are you with your sleep |  |  |  |  |  |
| 17(F10.3) | | How satisfied are you with your ablity to perform daily living activities ? |  |  |  |  |  |
| 18(F12.4) | | How satisfied are you with your capacity for work ? |  |  |  |  |  |
| 19(F6.3) | | How satisfied are you with yourself? |  |  |  |  |  |
| 20(F13.3) | | How satisfied are you with your personal relationships? |  |  |  |  |  |
| 21(F15.3) | | How satisfied are you with your sex life? |  |  |  |  |  |
| 22(F14.4) | | How satisfied are you with the support you get from your friends ? |  |  |  |  |  |
| 23(F17.3) | | How satisfied are you with the conditions of your living place? |  |  |  |  |  |
| 24(F19.3) | | How satisfied are you with your access to health services ? |  |  |  |  |  |
| 25(F23.3) | | How satisfied are you with your transport? |  |  |  |  |  |
|  | |  | **Never** | **Seldom** | **Quite often** | **Very often** | **Always** |
| 26(F8.1) | | How often do you have negative feelings such as blue mood, despair, anxiety, depression? |  |  |  |  |  |

Did someone help you to fill out this form ? ___________________________________________

How long did it take to fill this form out? _____________________________________________

Do you have any comments about the assessment ?______________________________________

## Appendix N: Health Related - Behavior Habit Fitness

**AYUSH COVID-19 PATIENT PROTOCOL 2020**

**HEALTH RELATED - BEHAVIOUR HABIT FITNESS**

**(HR-BHF)**

PATIENT NO: ________________PATIENT INITIALS :_____________DATE:__________

**Please put a vertical line across the scale to indicate your extent of the health related problem**

1. **Please consider the past ONE WEEK while answering. We want you to give your overall assessment.**
2. GENERAL HEALTH: How would you rate your overall general health?

100

0

Very Poor Very Good

1. How much is your anxiety ?

100

0

Very anxious No anxiety at all

1. Fatigue: How much do you feel tired in your daily routine?

100

0

Nil Feel very tired

1. How much is your Energy level?

100

0

Low energy Feel Energetic during my daily routine

1. How is your Bowel movement (passing stools/faeces)?

100

0

Highly irregular and unsatisfying Satisfactory and normal bowel habit

1. Are you stressed?

100

0

No Stress Maximum Stress

1. How happy are you?

100

0

Very Sad Very Happy

1. How do you rate your sleep?

100

0

Normal Bad and unable to sleep properly

1. How much is your appetite for food?

100

0

Nil Very Good

**THANK YOU FOR YOUR PARTICIPATION**

## Appendix O: Laboratory Diagnosis and Cytokine Assay

**LABORATORY DIAGNOSIS AND CYTOKINE ASSAY**

**The following laboratory investigations are proposed to be carried out as per the protocol on prophylaxis against COVID-19 in high risk health care providers and other risk prone individuals in the community**:

1. Diagnostic: nose/throat swab to detect COVID 19 using RT-PCR
2. Serology: specific anti-COVID IgM (ELISA) and IgG antibodies (chromatography)
3. Cytokine Assay: gamma Interferon, anti-TNF apha & beta, IL-6, IL-4, IL-13, IL-17, MCP
4. Routine Laboratory tests: detailed in protocol and in a separate Appendix

**Laboratory Diagnosis of Covid-19:**

Specific diagnosis of Covid-19 is done by specific molecular tests to determine one or several nucleic acid targets specific to SARS–CoV-2on respiratory samples (throat swab/ nasopharyngeal swab/ sputum/ endotracheal aspirates and bronchoalveolar lavage. The virus may also be detected in the stool and in the blood in severe cases. The tests that are currently used for diagnosis of SARS–CoV-2 identify viral RNA through nucleic acid amplification, usually using real time Reverse Transcriptase - Polymerase Chain Reaction (rRT-PCR) (1). Routine confirmation of cases of COVID-19 is based on detection of unique sequences of virus RNA by Nucleic Acid Amplification Test (NAAT) such as rRT-PCR with confirmation by nucleic acid sequencing when necessary. The viral genes targeted so far include the N, E, S and RdRP genes. The most common samples that are being tested are swabs taken from the nasopharynx and/or oropharynx. Nasopharangeal swabs are considered somewhat more sensitive than those taken from the oropharynx. (2). In case both are collected, the two swabs may be combined and tested to increase viral RNA extraction. Swabs are transported in universal viral transport medium immediately after sample collection to preserve viral nucleic acid. Samples taken from sputum, endotracheal aspirates, and bronchoalveolar lavage may have greater sensitivity than upper respiratory tract specimens (3). Inadequate sample collection may result in a false-negative test. All samples undergo RNA extraction followed by qualitative RT-PCR for target detection.The ability of a negative RT-PCR assays to rule out COVID-19 on the basis of upper respiratory tract samples obtained at a single time point remains unclear. Conversely, if a patient has had a positive test result, it is recommended obtaining at least 2 negative upper respiratory tract samples, collected at intervals of 24 hours or longer, to document SARS–CoV-2 clearance (4).

Indian Council for Medical Research – National Institute of Virology (ICMR-NIV) has completed evaluation of 20 non- US FDA EUA/CE IVD kits.

As per ICMR guidelines, currently first line screening for COVID-19 is being done using E gene Assay. All positive samples are sent to the reference laboratory (ICMR-NIV, Pune) for confirmatory testing. It is only after confirmatory test comes positive, that the sample is declared positive. Confirmatory assays available currently at ICMR-NIV are:

- ORF 1b
- RdRp gene assay
- E gene assay
- N gene assay

**Serology:**

Testing for different immunoglobulin (Ig) subclasses is common in serodiagnostics. As antibodies of IgM subclass are usually the first to develop following a primary challenge, IgM is considered to be a parameter of the early phase of infection. Serologic tests that identify antibodies (such as IgA, IgM, and IgG) to SARS–CoV-2 from clinical specimens such as whole blood, serum or plasma such as enzyme-linked immunosorbent assays, are less complex than molecular tests and have the potential to be used for diagnosis in certain situations especially when combined IgM ELISA assay with PCR for each patient compare with a single quantitative PCR(5). However, their utility for diagnosing acute infections is probably limited around the time of symptom onset, because the viral shedding and transmission risk seem to be highest at the pre-symptomatic or symptomatic stage (2). Antibody responses to infection may take a few days to weeks to be reliably detectable (5). Negative results would not exclude SARS–CoV-2 infection, particularly among those with recent exposure to the virus (6).

Serological surveys can aid investigation of an ongoing outbreak and retrospective assessment of the attack rate or extent of an outbreak. In cases where NAAT assays are negative and there is a strong epidemiological link to COVID-19 infection, paired serum samples (in the acute and convalescent phase) could support diagnosis once validated serology tests are available. Serum samples can be stored for these purposes. Also, rapid screening of SARS-CoV-2 carriers who are symptomatic or asymptomatic, in hospitals, clinics and diagnostic laboratories can be done using IgM-IgG combined assays that has shown relatively good specificity and sensitivity (7). Serology detection is also likely to play a role in determining the immunity of health care workers as the outbreak progresses.

**Cytokines:**

RATIONALE FOR CYTOKINE RESEARCH: Cytokine assay can be used to study important immune events of anti-viral (gamma interferon), pro-inflammatory (IL-6, anti-TNF, IL-17), TH 1 and TH 2 response and B cell activity (Il 4, IL 13), macrophage activation (MCP). Intense up regulation and elevation of IL 6 has been extensively reported by several clinical case series and research and a cause of ‘cytokine storm’ that often predates progressive severity and mortality. Other cytokines are also reported to be elevated. All these events are important in the pathophysiology of COVID 19 and may predate the onset of clinical infection. Also, it is important to know the baseline assay of these cytokines in healthy population. There is a dire need to generate normative data in the Indian population and this can be done in this research protocol. Without the latter, it may be difficult to evaluate modest elevations of cytokines. Although this is a protocol for prophylaxis, several patients may show elevations due to basal environmental conditions, asymptomatic COVID 19 infection, and pre-infection up regulated innate immune response. Also, it is expected that some study participants will contract COVID 19 infection and go on to develop the illness and require medical management. It may be useful to know the pre-illness cytokine status of these individuals and this may also be repeated during the illness to evaluate the immune response.

Cytokines play an important role in immunopathology of viral infections in which a rapid and coordinated innate immune response is often seen as the first line of defense against viral infection. However, dysregulated and excessive immune responses may cause immune imbalance leading to severe systemic inflammatory disorders. Pro-inflammatory responses have reported to play an important role in the pathogenesis of several viral infections (8) including Human Coronavirus (HCoVs)(9). A cytokine profile resembling secondary hemophagocyticlymphohistiocytosis (sHLH) is reported to be associated with COVID-19 disease severity, characterised by increased levels of cytokines and chemokines such as interleukin (IL)-2, IL-7, granulocytecolony stimulating factor, interferon-γ inducible protein 10, monocyte chemoattractant protein 1, macrophage inflammatory protein 1-α, and tumour necrosis factor-α (10). Elevated ferritin levels along with elevated interleukin-6 levels have been reported as significant predictors of fatality in a retrospective, multicentre study of 150 confirmed COVID-19 cases in Wuhan, China, suggesting that mortality might be due to virally driven hyperinflammation (11).High levels of expression of IL-1B, IFN-γ, IP-10, and monocyte chemoattractant protein 1 (MCP-1) have been reported in patients with COVID-19 (10). Positive correlation between serum levels of IL-2R and IL-6 (Cytokine storm) and severity of diseases has been seen in patients with COVID-19 (12). In COVID-19, the inflammatory cytokine storm is closely related to the development and progression of Acute Respiratory Distress Syndrome.

Cytokines can be estimated in the serum of patients by several assays such as ELISA or multiplex assays.  Advances in laboratory technologies including flow cytometrics, Luminex bead-based assays, planar multiplex assays. Although the multiplex platforms and ELISA-based systems exhibit distinct strengths and weaknesses, conventional quantitative ELISA assays are very convenient in clinical settings. Several sandwich ELISA assays using monoclonal antibodies against various cytokines are commercially available wherein the microwell plates are coated with monoclonal antibodies against the cytokine to be estimated in the serum.

**Covid-19 tests, times & utility.**

| **Type of Test** | **When to test** | **Whom to test** | **Action Required if tested positive** |
| --- | --- | --- | --- |
| Nucleic Acid Amplification Test (NAAT) by rRT-PCR | Viral load peaks at the end of first week after infection, just before and as symptoms are developing. It may be intermittent, so a single negative swab result can be misleading and tests may need to be repeated | Individuals with suspected current infection with SARS-CoV-2 | Quarantine to prevent transmission and monitor course of illness |
| Antibody detection (IgM and/or IgG by rapid lateral chromatography methods | Specific IgM antibodies start to become detectable after 4-5 days, with positive IgM in ~70% of symptomatic patients by 8-14 days and ~90% of total antibody tests positive by 11-24 days.  IgG reactivity is thought to reach >98% after several weeks, but duration of the response of this antibody is not yet know. | Individuals suspected with recent exposure to SARS-CoV-2 in arRT-PCR negative test result and who is asymptomatic. | Facilitate contact tracing & surveillance.  Identify those potentially immune to SARS-CoV-2. |

References

2. Zou L, Ruan F, Huang M, Liang L, Huang H, Hong Z, Yu J, Kang M, Song Y, Xia J, Guo Q, Song T, He J, Yen H-L, Peiris M, Wu J. 2020. SARS-CoV-2 viral load in upper respiratory specimens of infected patients. N Engl J Med 382:1177–1179. doi:10.1056/NEJMc2001737.
4. **European Centre for Disease Prevention and Control.** Novel coronavirus (SARS-CoV-). Accessedat <https://www.ecdc.europa.eu/sites/default/files/documents/COVID-19-Discharge-criteria.pdf>. Last accessed 14 April 2020.

## Appendix P: Classification of Adverse Events

**CLASSIFICATION OF ADVERSE EVENTS**

Adverse Events (AE):

All observed or volunteered adverse events regardless of treatment group or suspected causal relationship to study drug will be recorded on the AE Form. All AE’s must be classified according to their severity as Mild, Moderate and Severe.

For all AE, the investigator must pursue and obtain information adequate both to determine the outcome of the adverse event and to assess whether it meets the criteria for classification as a Serious AE.

Follow-up of the adverse event even after the date of therapy discontinuation, is required if the AE or its sequelae persist. Follow-up is required until the event or its sequelae resolve or stabilize at a level acceptable to the Investigator.

*Please note that AE are not limited only to adverse drug reactions. Any noxious event and or a medically important deviations from normality will be recorded as AE.*

Criteria for determining category of relationship of AE to trial treatment will be as follows:

1. Not related: AE’s which are definitely attributed to other causes.

2. Unlikely: (must satisfy at least two)

- It does not follow a reasonable temporal sequence from administration of the test drug
- It could readily have been produced by the patients clinical state, environmental or toxic factors, or other modes of therapy administered to the patient
- It does not follow a known pattern of response to the test drug
- It does not reappear or worsen when the drug is re-administered

3. Possible: (must satisfy at least two criteria) An AE may be considered possibly related if or when

- It follows a temporal sequence from administration of the drug
- It could not readily have been produced by the patient’s clinical state, environmental or toxic factors.
- It follows a known pattern of response to the test drug

4. Probable: (must satisfy three of the following)

- It follows a reasonable temporal sequence from administration of the drug
- It could not be reasonably explained by the known characteristics of the patient’s clinical state, environmental or toxic factors, or other modes of therapy administered to the patient
- It decreases or disappears on cessation or reduction in dose.
- It follows a known pattern of response to the test drug

5. Definitely (must satisfy all four criteria)

- It follows a reasonable temporal sequence from administration of the drug
- It could not be reasonably explained by the known characteristics of the patient’s clinical state, environmental or toxic factors, or other modes of therapy administered to the patient
- It decreases or disappears on cessation or reduction in dose and recurs with re-exposure to drug.
- It follows a known pattern of response to the test drug

f) Serious Adverse events (SAE):

All serious adverse events which occur during the study until the last follow-up visit required by the protocol, regardless of treatment group or suspected relationship to drug, must be reported immediately by telephone \ fax to Principal Investigator***,*** .

SAE include those that suggest a significant hazard, such as events which:

- are fatal
- result in permanent disability
- require in – patient hospitalization or a hospital stay
- are life – threatening
- a congenital anomaly or drug overdose

It should be emphasized that, regardless of the above criteria, any additional adverse experience which the investigator considers serious should be immediately reported.

For all serious adverse events, the investigator is obligated to pursue and provide information as requested, in addition to that on the case record form. In general, this will include a description of the adverse event in sufficient detail to allow for a complete medical assessment. The investigator should ensure that information on such cases is reported by telephone or by other means and information entered in the case record form is accurate and consistent.

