**11.2 Secondary Efficacy:**

1) Rate of patients with negative SARS-CoV-2 on nasal or throat swab in a 2-day continuous real time RT-PCR test beginning from ‘first day of clinical recovery’ (see above) or ‘Day 10 after onset of symptoms depending on whichever of the two time points is first achieved

2) Timelines (days counted from onset of illness) - normal body temperature <37◦C, absence or minimal cough (see ‘clinical recovery’ for the definition), absence of dyspnoea (respiration rate 24/minute or less on room air), onset of clinical pneumonia, pneumonia diagnosed on chest X-Ray or CT scan, time to supplemental oxygen, admit in intensive care unit, mechanical ventilation (non-invasive), mechanical ventilation (invasive), steroid use, respiratory failure, adult respiratory distress syndrome, cytokine storm syndrome, secondary infection, shock, septicaemia shock, hospital discharge, death, negative nose or throat swab confirmatory test, all-cause mortality (Time Frame: up to 28 days).

Note: In case of symptoms, the absence on improvement should be sustained for at least 72 hours or live hospital discharge, whichever comes first.

3) Proportion OF patients developing an event that reflects clinical or otherwise improvement of worsening (the events are similar to those listed under Timelines, see above)

4) Improvement on pulmonary function tests using simple ‘home expiratory spirometer’ device and peripheral pulse oximetry

5) Improvement in selected laboratory parameters: blood haemoglobin, differential and total leukocyte counts, liver enzymes, renal functions, acute phase reactants, serum IL-6 and other selected cytokines, serum muscle enzymes (CK, CPK), serum ferritin, serum d-Dimer, anti-oxidant markers, serum BNP (cardiac function)

6) Serological Protective Antibody Assay (IgM and IgG)

7) Radiological Improvement on digital chest Xray and HRCT chest

8) Drug related: side effects and toxicity, and tolerability

9) Health status: WHO QOL (Appendix M) brief, health related behaviour habit and fitness questionnaire based on visual analogue scale (See Appendix N)

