**CLINICAL STUDIES OF AYUSH 64**

1. The report on management of Chikungunya through Ayurveda and Siddha has documented the efficacy of ‘AYUSH-64’. (Anonymous. Management of Chikungunya through Ayurveda and Siddha, A Technical Report, CCRAS, Dept of AYUSH, MoHF&W, Govt of India, 2009)
2. Clinically effective in cases of Microfilariasis. (40)
3. 81% curative effect on Plasmodium vivax, drug is more effective in ring stage than in Gamete stage. In the cases of mixed infection of P. vivax & P. falciparrum the curative effect was found to be 75% after longer therapy. (41)
4. Clinically shown good effect in the management of microfilaraemia (42, 43)
5. In a study with about 4500 participants, Ayush-64 was found safe and nontoxic with good antimalarial activity and also observed that by giving Ayush-64 to all fevers along with anti- mosquito measures, there was a decline in the infectivity rate. (44)
6. A double-blind study demonstrated comparative efficacy of AYUSH 64 to the chloroquine /primaquine as the standard modern control in sixty cases of P. Vivax malaria. (45)
7. In a prospective, open-label, nonrandomized, single group, single-centre pilot study with pre-test and post-test design one-week intervention of ‘AYUSH 64’ in a dose of 3gms/day effectively helped to recover from Influenza Like Illness  symptoms and return to normal life early with reduced frequency of usage of acetaminophen/ antihistaminic. No adverse effects were found during the study (46).
8. A pilot study done on 112 participants produced 97.14% result with prophylactic treatment in P.F. Malaria (47)

**Note: The drug /drug and drug herb interactions may not be so relevant as the formulation is not NCE /and possess herbs processed as per Standard procedures of Ayurveda, however such studies may be taken up simultaneously**

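### Appendix P's causality rule can force the label Unlikely on an event that recurs on re-exposure, and gives other events contradictory labels with no order of precedence

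*Combined protocol and SAP*

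**What the plan says.** Appendix P has five causality categories. Not Related is a direct judgement; the other four are reached by counting criteria.

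- **Unlikely** reads "Unlikely: (must satisfy at least two" of four. The first is the absence of plausible timing after dosing. The second is a ready alternative cause: "It could readily have been produced by the patients clinical state, environmental or toxic factors, or other modes of therapy administered to the patient". The third is that the reaction matches no recognised pattern for the drug. The fourth concerns re-exposure: "It does not reappear or worsen when the drug is re-administered".
- **Possible** reads "Possible: (must satisfy at least two criteria" of three: timing, no ready alternative cause, known pattern. Its alternative-cause criterion leaves out other treatments given to the patient, which Unlikely includes.
- **Probable** needs three of four: timing, no alternative cause, improvement on stopping or reducing the dose, known pattern.
- **Definitely** needs all four. The criteria resemble those of Probable, but the one on stopping also requires recurrence on re-exposure.

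No sentence says which category applies when an event qualifies for more than one.

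Section 11.2, item 8 lists as an outcome "Drug related: side effects and toxicity, and tolerability", and section 4 puts safety in the primary objective. The form in Appendix Q records relatedness as Yes or No, and nothing maps the five categories onto it. Appendix P also says that all adverse events are recorded, and all serious ones reported, whatever their suspected relationship to the drug. Section 17.2 tests the proportion of patients with an adverse event and states no causality filter.

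**The concern.** Good timing, improvement on stopping and recurrence on re-exposure are together the strongest evidence that an individual case can offer for a drug effect. A rule that can return Unlikely for such a case, and nothing higher, works against its own purpose. A rule that lets one event be both Unlikely and Probable leaves the label to whoever applies it, and this is a multicentre, open-label trial.

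The two conditions behind the forced label are plausible here. Every patient has acute COVID-19, and section 5 expects standard of care to vary between sites and patients, so an alternative explanation will often be available. An unexpected reaction has, by its nature, no known pattern. For AYUSH 64, the influenza-like-illness pilot cited in Appendix D supplies none: "No adverse effects were found during the study".

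At stake is the consistency of any count of drug-attributed events. That count would also be too low if Unlikely is read as unrelated.

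**Working it through.** The documents state no figure on this point, so there is nothing to reproduce. The check applies the Appendix P rules as logic.

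**Inputs (all Appendix P).** T = reasonable timing; A = ready alternative cause; K = known pattern; D = improves on stopping; R = re-exposure positive, negative or not done. Each of T, A, K and D is 1 for yes and 0 for no.

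**Formulas.**
- Unlikely score = (1 − T) + A + (1 − K) + [R negative]; met at 2 or more of 4.
- Possible score = T + (1 − A) + K; met at 2 or more of 3.
- Probable score = T + (1 − A) + D + K; met at 3 or more of 4.
- Definitely score = T + (1 − A) + [D = 1 and R positive] + K; met at 4 of 4.

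**Step 1: event with T = 1, D = 1 and R positive.**

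| Alternative cause | Known pattern | Unlikely | Possible | Probable | Definitely |
|---|---|---|---|---|---|
| no | yes | 0 of 4 | 3 of 3, met | 4 of 4, met | 4 of 4, met |
| no | no | 1 of 4 | 2 of 3, met | 3 of 4, met | 3 of 4 |
| yes | yes | 1 of 4 | 2 of 3, met | 3 of 4, met | 3 of 4 |
| yes | no | 2 of 4, met | 1 of 3 | 2 of 4 | 2 of 4 |

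Only the last row is forced into Unlikely. There the positive re-exposure adds nothing to Possible or Probable and cannot complete Definitely.

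**Step 2: overlaps.** Let f be how many of these three hold: no timing, alternative cause, no known pattern. The Unlikely score is f + r, with r = 1 if re-exposure is negative and 0 otherwise. The Possible score is 3 − f. Both are met when f ≥ 2 − r and f ≤ 1.
- r = 0 (positive or not done): f would have to be at least 2 and at most 1, so there is no overlap.
- r = 1 (negative): f = 1. That is 3 ways × 2 values of D = 6 of 2⁴ = 16 patterns. The Probable score is then 2 + D, so the 3 patterns with D = 1 meet Probable as well.

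**Step 3: the wording gap.** Step 2 treats the alternative-cause criteria of Unlikely and Possible as mirror images, which they are not. Take an event explainable only by a standard-of-care drug, with correct timing and no known pattern. Unlikely scores 2 of 4 (other treatment, no pattern). Possible scores 2 of 3 (timing, and not readily due to clinical state, environment or toxic factors). Both are met whatever the re-exposure result. So the absence of overlap at r = 0 does not extend to standard-of-care causes. Probable does name other treatments, so it scores at most T + D = 2 of 4 and is not met.

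**Step 4: does the obvious repair work?** Barring Unlikely after positive re-exposure is not enough by itself. The last row of the table would then meet no counted category (1 of 3, 2 of 4, 2 of 4). A minimum category has to be stated as well.

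**The case against.** The strongest reply is that the consequences are small. Section 18.3 and Appendix P require every adverse event to be recorded irrespective of causality, serious events are reported whatever the relationship, section 17.2 compares patients with adverse events without a causality filter, a DSMB reviews adverse events, and section 14 adopts the CONSORT harms extension. All of this stands. A reader might infer that the rule under-counts drug-related harm in general, but the documents do not support that. Only a count of attributed events could move. It would be too low only if Unlikely is treated as unrelated, and the plan gives no such mapping.

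The second reply is that the forced profile is unusual. An event that stops and recurs with the drug is hard to describe as readily explained by COVID-19. Dosing runs for 12 weeks, while section 8 expects most patients home within 5 to 15 days, so much exposure falls after the acute illness. Nor are the formulations without documented effects: Appendix D describes one AYUSH 64 ingredient as purgative and another as laxative, Appendix E describes liquorice components as inhibitors of cortisol metabolism, and section 14 promises investigators a checklist of common drug-related effects. This limits how often the case would arise; it does not make the rule coherent. Although no re-exposure procedure is specified, Appendix K provides for therapy interruptions with start and end dates, so such information can arise.

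The third reply is that 6 of 16 (38%) is not a magnitude. That is correct: it counts cells of a logical grid, and only those with negative re-exposure.

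**Conclusion.** The defect is real but narrow. Appendix P is internally inconsistent in three ways:

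- Recurrence on re-exposure earns nothing below Definitely and does not override Unlikely. In 1 of 4 combinations, an event with correct timing, improvement on stopping and recurrence can be classed only as Unlikely. It would be wrong to infer that every such event is so labelled; the other three reach Probable or Definitely.
- With negative re-exposure, 6 of 16 patterns meet both Unlikely and Possible, 3 of them also Probable, and no rule says which prevails.
- Events explainable only by a standard-of-care drug, well timed and without a known pattern, meet both Unlikely and Possible, because Possible omits other treatments. This assumes that toxic factors does not itself cover such drugs; Unlikely lists the two separately.

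Drug-attributed counts under section 11.2, item 8 may therefore be inconsistent, and too low if Unlikely is read as unrelated. How often this would happen cannot be derived from the documents.

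**What to change.** Amend Appendix P as follows:

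1. Assess from Definitely downwards and assign the highest category met. This settles the six overlaps: three become Probable and three Possible.
2. State that an event with a reasonable temporal sequence that recurs on re-exposure cannot be Unlikely and is at least Possible. Do not extend this to improvement on stopping alone: COVID-19 symptoms usually resolve anyway, so natural recovery would be attributed to the drug, and only in the arm that receives it. The rule classifies re-exposure information where it exists; it does not call for re-exposure.
3. Use the same alternative-cause wording in Unlikely and Possible. Adding other treatments to Possible would also match Probable and Definitely.
4. State which categories count as related on the Yes/No form in Appendix Q, and so in section 11.2, item 8. That form's relatedness fields name Ashwagandha and Hydroxychloroquine, neither of which is an investigational drug here, so the form and the protocol need to be reconciled at the same time.

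Section 17.2 needs no new analysis, since the comparison of patients with adverse events is already there. The cost is a few lines of wording, with no new data or visits. The downside is that slightly more events will be reported as possibly drug-related.
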